## Abstract

**Background:**

Insomnia is the most common comorbidity in children with autism spectrum disorder (ASD) and seriously affects their rehabilitation and prognosis. Thus, an intervention targeting insomnia in ASD seems warranted. Repetitive transcranial magnetic stimulation (rTMS), a potentially effective treatment for improving sleep quality and optimizing sleep structure, has already been demonstrated to alleviate insomnia symptoms and sleep disturbance in different neurological and neuropsychiatric conditions. This trial aims to investigate the effects of rTMS on insomnia in patients with ASD.

**Method:**

This study is designed to be a double-blind, randomized, and sham-controlled trial with a target sample size of 30 participants (aged 3–13 years) diagnosed with ASD comorbid with insomnia. The intervention phase will comprise 20 sessions of rTMS or sham rTMS applied over the right dorsolateral prefrontal cortex (DLPFC) within four consecutive weeks. The effect of rTMS on insomnia and other symptoms of ASD will be investigated through home-PSG (two consecutive overnights), sleep diary, CSHQ, CARS, ABC, SRS, RBS-R, and metabolomics analysis at baseline and posttreatment. A follow-up assessment 1 month after the intervention will examine the long-term effects.

**Discussion:**

The results of this study may address an important knowledge gap and may provide evidence for the use of rTMS to treat insomnia in ASD. Furthermore, it will elucidate the potential mechanism and link between sleep disorders and clinical symptoms.

**Clinical trial registration:**

The study is ongoing and has been registered at the Chinese Clinical Trial Registry (ChiCTR2100049266) on 28/07/2021.

## Introduction

Autism spectrum disorder (ASD) is a group of neurodevelopmental disorders with significant clinical heterogeneity characterized by social communication deficits and restricted, repetitive sensory–motor behaviors (1, 2). The prevalence of ASD has increased to 1/59, and over 70% of individuals with autism have developmental problems (intellectual disability, etc.), general medical issues (sleep disturbances, gastrointestinal problems, etc.), psychiatric conditions (anxiety and depression, etc.), or personality disorders (schizoid personality disorder, etc.) to varying degrees (2, 3).

Among these comorbidities, sleep disturbances, especially insomnia, are the most common conditions, and their prevalence in ASD is 40–80%, which is two to three times higher than that in the general population (4–6). Previous studies have found a bidirectional association between ASD and sleep disturbances (7). Furthermore, like the core symptoms of autism, insomnia may persist throughout life and can not only predict the severity of core symptoms and related daily behavior problems, such as tantrums and aggression, but also affect the health and wellbeing of parents (6, 8). Given the significant adverse impacts, treating insomnia has therefore been a primary therapeutic goal.

Over the years, lifestyle modifications, behavioral interventions, and pharmacological therapies have been adopted for treating sleep disturbances in ASD (9, 10). Among them, cognitive behavioral therapy for insomnia (CBT-I), as a first-line treatment to manage chronic insomnia, has also been used to treat sleep disturbances in children with ASD. One study of school-aged children with high-functioning ASD demonstrated that CBT-I was a feasible and promising treatment to improve the sleep and function of children and parents (11). Nevertheless, poor treatment responses (25%) were reported in ASD with parent-directed behavioral sleep interventions due to numerous ASD children having atypical cognitive profiles, such as impaired social cognition and atypical perceptual and information processing, which led to poor cooperation during the treatment (12, 13). As a stepwise approach to sleep disturbances, pharmacotherapy is often provided when behavioral intervention fails. Nevertheless, there are no medications with regulatory approval by the Food and Drug Administration (FDA) for the treatment of insomnia in ASD (9). Considering the severity of sleep problems, drugs including antidepressants, antipsychotics, benzodiazepines, and melatonin have been used off-label in the clinic with some potential side effects (14, 15). From the perspective of the parents, behavioral and nonpharmacological interventions are generally the first choice over equally effective medication (9). However, existing treatments are less effective. Therefore, identifying a safe and effective nonpharmacological treatment for insomnia in children with ASD is an urgent matter.

Repetitive transcranial magnetic stimulation (rTMS) is a noninvasive therapy that produces a magnetic field and introduces excitatory or inhibitory cortical excitability in the brain below the magnetic coil by modulating different stimulus frequencies (16). rTMS has been used to treat major depression and treatment-resistant depression (17). Recently, numerous studies have adopted high- or low-frequency rTMS protocols with positive results in in hemiparesis due to pediatric stroke, mild traumatic brain injury, and tics/Tourette syndrome (18, 19). However, despite the benefits demonstrated for adult migraine, rTMS has been insufficiently studied for migraine in children. In addition, evidence for rTMS in childhood epilepsy and ADHD remains mixed (19). In ASD, the results confirmed that by stimulating different brain regions, different clinical symptoms were correspondingly improved: stimulating the dorsal lateral prefrontal cortex (DLPFC) can improve irritability, repetitive behaviors, and executive functioning; stimulating primary motor cortices can improve motor behavior; stimulating the medial prefrontal cortex can improve mentalizing; and stimulating the premotor cortex can improve speech production and eye-hand coordination (20). Regarding the adverse effects of TMS in children, studies found that the overall rate of the adverse effects, including headache, facial discomfort, irritability, pain at the application site, headedness, and dizziness, is 25% (18, 19, 21). However, all these adverse effects are mild and transient and can be resolved after rest or medication (21).

Moreover, meta-analysis and systematic reviews have indicated that low-frequency rTMS applied to the dorsolateral prefrontal cortex is safe and has the potential to alleviate insomnia symptoms and sleep disturbance in different neurological and neuropsychiatric conditions (22–24). Studies have found that rTMS not only improves sleep quality and optimizes sleep structure but also maintains therapeutic efficacy over pharmacological treatments and cognitive behavioral therapy and has emerged as a promising tool for treating sleep disturbances (22). Moreover, after 10 daily sessions of rTMS treatment in patients with primary insomnia, the concentrations of serum GABA and brain-derived neurotrophic factor (BDNF) were significantly higher than baseline (25). As we already know, GABA and BDNF both have a close relationship with sleep regulation (26–28). The change in metabolomics may be the potential mechanism of rTMS treatment in alleviating insomnia (28).

However, the implications of rTMS for insomnia in ASD patients have not been fully established. Only one study indicated that rTMS can alleviate sleep disturbances in ASD, which were assessed by the Children's Sleep Habits Questionnaire (CSHQ) (29). No randomized, double-blind, controlled studies were conducted to evaluate the efficacy of rTMS for insomnia through objective assessments such as PSG or actigraphy. Therefore, we aim to conduct a randomized, double-blind, sham-controlled trial to explore the effect of rTMS on insomnia with an objective assessment of ASD. Additional objectives include explorations of the effects of rTMS on ASD symptoms and the association between insomnia and ASD symptoms. We hypothesize that 1) rTMS applied to the right dorsolateral prefrontal cortex (DLPFC) can alleviate sleep quality and ASD symptoms and 2) metabolic changes may play a mediating role in sleep quality and ASD symptoms.

## Methods and analysis

### Study design and settings

This is a double-blind, sham-controlled pilot trial to examine the efficacy of rTMS on insomnia in ASD. Participants will be randomized to the rTMS group or sham rTMS group for 4 weeks (5 days/week). Assessments of the primary and secondary outcomes will be performed at baseline, after the 4-week treatment, and at the 4-week follow-up with rTMS or sham treatment (Figure 1). The protocol was approved by the Biomedical Research Ethics Committee West China Hospital of Sichuan University and is registered at the Chinese Clinical Trial Registry (ChiCTR2100049266).

**Figure 1 F1:**
[figure not shown]
Time schedule of screening, interventions, assessments and visits of participants.

### Participants

Participants will be recruited from the special education schools, nursery and primary schools, the second outpatient department of the West China Mental Health Center of Sichuan University, and online. Measurements and interventions will be carried out at the second outpatient department of the West China Mental Health Center of Sichuan University.

### Sample size

Previous studies in patients with insomnia have shown that rTMS treatment can decrease sleep onset latency by at least 17.88–44.8 min (30, 31). According to previous studies, the minimally important difference of the primary outcome (sleep onset latency) is assumed to be 10 min (SD, 8.4 min) (32). To detect this difference with a two-sided significance level of 0.05 and a power of 80%, and account for the drop rate of 10% according to existing rTMS studies in autism (33, 34), a total of 30 participants will be included (PASS, version 15).

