### Randomization and blinding

For participant allocation, a computer-generated random list will be used, which is based on the permutation block method with a random number generator and allocated at a ratio of 1: 1. A research assistant concealed the allocation sequence using sealed, opaque envelopes that contain the treatment information (A or B) before officially entering the study. After completing the consent form and baseline measures, the corresponding envelope for a given participant ID will be given to the rTMS therapist prior to the first rTMS session. The rTMS therapist is the only person who determines the treatment method (rTMS or sham treatment) for A or B. Once the treatment information is decided, no change will be accepted. Others, such as study investigators, parents, patients and statistical analysts, will be completely blinded to the treatment condition. Any adverse effects or body discomfort will be recorded after each rTMS treatment session. The aforementioned individuals will be unblinded to information about the treatment only when a participant experiences serious adverse events, and then an independent investigator will reveal the current treatment of this participant.

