### Outcomes

The primary outcome of this study will be the difference in sleep onset latency between baseline and the end of treatment. Secondary outcomes will be differences in other parameters derived from polysomnography, the sleep diary, CSHQ, CARS, ABC, SRS, RBS-R, and metabolomics analysis.

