## Statistical analysis

We will use SPSS software version 26.0 (IBM Corp, Armonk, New York, US) to perform data analysis. Demographic and baseline data will be analyzed with standard descriptive statistics. Normally and non-normally distributed data will be presented as means (SDs) and medians (quartiles), respectively. The comparison of basic data between the rTMS group and sham rTMS group will be performed using Student's *t*-test, the chi-squared test, or the nonparametric test according to the data type. To verify the efficacy of our intervention, the final analysis will be conducted according to the intent-to-treat (ITT) principle, and missing data will be replaced by means of the last observation carried forward rules. Changes in quantitative variables over time (evaluation of the therapeutic effect of rTMS on variations in sleep latency) will be analyzed using random-effect models allowing us to take into account repeated measurements. Time (baseline, post, and 1-month follow-up) and group (rTMS or sham) effects will be estimated and tested, along the interaction with the group. According to the same strategy, changes in other quantitative variables over time will be investigated. To further analyze the relationship between the change in the parameter of sleep and clinical symptoms, logistic regression, general linear correlation or regression will be taken into consideration between various types of outcomes. The number and proportions of participants with side effects, adverse events, and serious adverse events will also be reported. All statistical analyses will be two-sided, and statistical significance will be set at p<0.05. For untargeted metabolomics analysis, principal component analysis (PCA) and partial least squares discriminant analysis (PLS-DA) will be performed in metaX (a flexible and comprehensive software for processing metabolomics data). We will apply univariate analysis (*t*-test) to calculate the statistical significance (*P* value). Metabolites with VIP > 1 and *P* value < 0.05 and fold change (FC)≥ 2 or FC ≤ 0.5 will be considered to be differential metabolites.

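### The sample size does not say whether the 8.4 min SD is that of sleep onset latency or of its change; if of latency, the planned change-from-baseline contrast reaches 80% power only at a baseline-to-post correlation of about 0.37 to 0.46

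*Protocol article*

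**What the plan says.** Three sections of the protocol article bear on this point.

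- **Sample size:** "the minimally important difference of the primary outcome (sleep onset latency) is assumed to be 10 min (SD, 8.4 min". The calculation uses a "two-sided significance level of 0.05" and 80% power. It is said to "account for the drop rate of 10% according to existing rTMS studies in autism", and concludes that "a total of 30 participants will be included (PASS, version 15". Under Randomization and blinding, participants are "allocated at a ratio of 1: 1".
- **Outcomes:** "The primary outcome of this study will be the difference in sleep onset latency between baseline and the end of treatment".
- **Statistical analysis:** the primary variable, like the other quantitative outcomes, "will be analyzed using random-effect models allowing us to take into account repeated measurements". The terms of that model are then set out as follows: "Time (baseline, post, and 1-month follow-up) and group (rTMS or sham) effects will be estimated and tested", together with their interaction. No baseline covariate and no constraint of equal baseline means is mentioned.

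Two further statements affect how many participants are analysed. The Statistical analysis section specifies intention-to-treat with last observation carried forward. The Trial status section says data collection continues until 30 participants have completed treatment and the pre- and post-measurements.

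**The concern.** The sample-size sentence names the sized quantity as sleep onset latency, whereas the quantity tested is its change. The two have different SDs. If latency has the same SD at both visits and correlation rho between them, the variance of the change is 2(1 - rho) times the variance of latency. It is the larger of the two whenever rho is below 0.5.

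In the planned model, with baseline as an outcome time and baseline means free to differ between arms, the baseline-to-post interaction contrast carries that change-score variance. So if 8.4 min describes latency at one visit, the 80% power depends on a correlation that the article never states.

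A low correlation cannot be ruled out. Visits are about four weeks apart in children aged 3 to 13. For eligibility, the home PSG is read mainly from the second of two nights; if the outcome is read the same way, each visit rests largely on one night. Entry also requires latency above 20 min or wake time above 20 min, and selection on latency restricts the baseline range and tends to lower rho.

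**Working it through.** **Inputs from the article.** Difference 10 min, SD 8.4 min, two-sided 0.05, power 80%, dropout 10%, 1:1 allocation, total 30.

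**Assumptions.** Equal SD at baseline and week 4. Rho is not given, so a range is shown. Analysed per arm: 13 (the number behind the calculation) to 15 (all 30 analysed under carry-forward, or 30 completers as in Trial status).

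**Step 1: reproduce the 30.** For a two-sample t-test, the noncentrality is 10 / (8.4 × √(2/n)) with 2n - 2 degrees of freedom.

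- n = 12 per arm: power 79.6%.
- n = 13 per arm: 10 / (8.4 × √(2/13)) = 3.04 on 24 df, power 82.9%.
- 13 / 0.9 = 14.4, so 15 per arm and 30 in total. The stated figure is reproduced.

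This calculation uses 8.4 whatever it describes, so reproducing 30 does not show which SD was meant.

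**Step 2: if 8.4 min is the SD of change.** Power is 82.9% with 13 per arm and 88.2% with 15. No condition on rho arises.

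**Step 3: if 8.4 min is the SD of latency at one visit.** SD of change = 8.4 × √(2(1 - rho)).

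| rho | SD of change (min) | Power, 13 per arm | Power, 15 per arm | Total N for 80%, with 10% dropout |
|---|---|---|---|---|
| 0 | 11.88 | 54% | 61% | 54 |
| 0.2 | 10.63 | 63% | 70% | 44 |
| 0.3 | 9.94 | 69% | 76% | 38 |
| 0.4 | 9.20 | 76% | 82% | 34 |
| 0.5 | 8.40 | 83% | 88% | 30 |

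The largest SD of change that still gives 80% power is 8.73 min with 13 per arm and 9.44 min with 15. Solving for rho:

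- 13 per arm: 1 - 8.73² / (2 × 8.4²) = 0.46.
- 15 per arm: 1 - 9.44² / (2 × 8.4²) = 0.37.

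A random-intercept fit that pools residual variance over three visits would gain some degrees of freedom. The limiting normal-approximation thresholds are 0.41 and 0.32, so the conclusion is unchanged.

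**Step 4: adjust for baseline, SD of latency = 8.4.** Residual SD = 8.4 × √(1 - rho²). Estimating the covariate costs one degree of freedom and, on average, inflates the variance of the group difference by 1 + 1/(2n - 4): 1 + 1/22 = 1.045 at 13 per arm, and 1 + 1/26 = 1.038 at 15.

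| rho | Residual SD (min) | Power, 13 per arm | Power, 15 per arm |
|---|---|---|---|
| 0 | 8.40 | 81% | 87% |
| 0.3 | 8.01 | 85% | 90% |
| 0.4 | 7.70 | 87% | 92% |
| 0.5 | 7.27 | 91% | 94.5% |

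**Step 5: adjust for baseline, SD of change = 8.4.** Residual SD = 8.4 × √((1 + rho)/2), which never exceeds 8.4. At rho = 0.5 it is 7.27 min, with the same 91% and 94.5%. At rho = 0.9 it is 8.19 min, with 83% and about 88.5%, level with the unadjusted figures. Only as rho approaches 1 does the covariate cost show, and power then still tends to 81% and 87%.

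**The case against.** The strongest reply is that 8.4 min is already the SD of change. The sample-size sentence attaches it to the primary outcome, the Outcomes section defines that outcome as a change, and the preceding sentence under Sample size concerns reductions in latency under rTMS. On that reading nothing is underpowered. This stands as a possibility. Only the cited source could settle it, and the article does not report what that SD describes.

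Second, a threshold of 0.46 alone would be too severe, because carry-forward and the Trial status rule both point to 30 analysed. This also stands, which is why the threshold is given as a range. The 15-per-arm figures are the favourable end: a dropout whose baseline is carried forward contributes a change of zero.

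Third, a repeated-measures model with a group-by-time interaction is valid and unbiased under randomisation, it matches a change outcome, and an unseen analysis plan may specify baseline adjustment. All of this is fair. Leaving out a baseline covariate is not an error of validity. It matters here because, on one reading of the SD, the contrast as described does not secure the stated power.

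A reader might infer more than the article supports:

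- That the trial is definitely underpowered. This takes the single-visit reading as fact.
- That 30 can be reached only if 8.4 is the SD of change. Step 1 shows otherwise.
- That 8.4 min is too small, with far lower power at larger SDs. The article gives no larger SD, and that is a separate question.

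**Conclusion.** The point holds in conditional form. The article fixes a sample size on an SD whose basis it does not state, and describes an unadjusted change contrast for the primary outcome.

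If 8.4 min is the SD of change, the stated power is met. If it is the SD of latency at one visit, power is 54% to 61% at rho = 0 and 69% to 76% at rho = 0.3, and 80% needs rho of about 0.37 (15 analysed per arm) to 0.46 (13 per arm).

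These figures assume equal SDs at both visits, a true difference of 10 min, and a two-sample comparison of changes. The correlation is an assumption throughout. Baseline adjustment meets 80% on both readings for any rho from 0 up, provided 8.4 min is right for whichever quantity it describes.

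**What to change.** **Statistical analysis section.** Make the primary estimate the rTMS minus sham difference in sleep onset latency at the end of treatment, from the repeated-measures model of the post-treatment values (week 4 and follow-up) with group, time, their interaction, and baseline sleep onset latency as a covariate. Keeping baseline as an outcome time but constraining its mean to be equal across arms serves the same purpose. Settle this before any unblinded analysis.

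**Sample size section.** Say whether 8.4 min is the SD of latency at one visit or of its change from baseline, state the correlation assumed, and describe the 80% power as that of the baseline-adjusted week-4 contrast.

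**Cost.** One line of model wording, one or two sentences under Sample size, and one degree of freedom. Baseline home PSG is already scheduled for every participant in Table 1, so no extra participants, visits or measurements are needed.

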### Inclusion/exclusion criteria

Participants eligible for the trial must comply with all of the following:

1) A preliminary clinical diagnosis using DSM-5 in the Mental Health Center by a child psychiatrist will be confirmed by two well-trained child psychiatrists using the Autism Diagnostic Interview-Revised (ADI-R) and Autism Diagnostic Observational Schedule (ADOS-2) (35, 36).2) Age between 3 and 13 years.3) Patients with ASD must meet the following diagnostic criteria for insomnia in the International Classification of Sleep Disorders–Third Edition (ICSD-3) (duration > 3 months: difficulty sleeping (sleep latency > 20 min or wake-up time > 20 min after falling asleep) at least 3 nights per week, confirmed by sleep diary (at least 7 days) and portable home-PSG (2 consecutive nights, based mainly on the second-day monitoring data) (37).4) Not taking any drugs that affect sleep or no change in the drug dose and not taking new drugs during the trial period.5) Two living parents who are able to cooperate in signing the informed consent form and documents pertaining to related scales.

Participants will be excluded from the trial if they comply with one of the following:

1) Those who have a history of epilepsy or severe head trauma, who have medical device implants (such as pacemakers, etc.).2) Participants cannot cooperate.3) Severe neurologic or psychiatric disorders or medical conditions (e.g., skull defect and craniotomy) or other disorders likely to have an impact on sleep.

Participants who cannot tolerate the side effects (headache, etc.), develop any adverse events (seizure, etc.) during the treatment, or miss more than two rTMS treatment sessions in a row, or miss more than four sessions in total, will be withdrawn from this study.

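### Children may enter on night waking alone, but the trial is powered and tested on sleep onset latency, so the 80% power to detect 10 min depends on an unstated case mix

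*Protocol article*

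**What the plan says.** Under Inclusion/exclusion criteria, the insomnia criterion is "difficulty sleeping (sleep latency > 20 min or wake-up time > 20 min after falling asleep) at least 3 nights per week". The two limbs are joined by 'or'. The same item then says how the criterion is checked: "confirmed by sleep diary (at least 7 days) and portable home-PSG (2 consecutive nights, based mainly on the second-day monitoring data"). The diary and the PSG confirm the either/or rule, and no other criterion sets a minimum latency.

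Under Outcomes: "The primary outcome of this study will be the difference in sleep onset latency between baseline and the end of treatment". Other PSG parameters, which would include wake time after sleep onset, are secondary.

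Under Sample size, "the minimally important difference of the primary outcome (sleep onset latency) is assumed to be 10 min (SD, 8.4 min"). The calculation uses "a two-sided significance level of 0.05 and a power of 80"%, is inflated to "account for the drop rate of 10% according to existing rTMS studies in autism", and concludes that "a total of 30 participants will be included (PASS, version 15"). The same section cites latency reductions of at least 17.88 to 44.8 min in earlier rTMS studies of patients with insomnia.

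Under Randomization and blinding, children are "allocated at a ratio of 1: 1". Under Statistical analysis, the final analysis follows intention to treat with last observation carried forward, and baseline latency enters the random-effects model as one of three repeated time points.

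**The concern.** The eligibility rule, the primary outcome and the power calculation do not describe the same children. A child who qualifies only by night waking has, by the plan's own cut-off, a latency of about 20 min or less on most nights. At a baseline below 10 min, a 10-min fall is impossible. Between 10 and 20 min, it means losing half or more of the latency, over and above any change under sham. Yet the 10-min difference is applied to everyone, and intention to treat keeps these children in the primary comparison.

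If a material share enters this way, the average effect is diluted and the spread in the active arm widens. A null result would then be hard to read: it could mean that rTMS does not shorten latency, or that part of the sample did not have the symptom being measured.

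**Working it through.** **1. Reproduce the plan's figure.** Inputs from Sample size: difference 10 min, SD 8.4 min (taken as the SD of the quantity compared), two-sided 0.05, power 80%, drop-out 10%. Allocation is 1:1.

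- Normal approximation: n per arm = 2 × (1.96 + 0.842)² × 8.4² / 10² = 11.1, rounded up to 12.
- Noncentral t: 12 per arm gives 79.6% and 13 per arm gives 82.9%, so 13 are needed.
- Drop-out: 13 / 0.9 = 14.4, rounded up to 15 per arm, or 30 in total.

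The stated 30 is reproduced from its own inputs.

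**2. Add the case mix.** Let f be the share entering on waking alone, e their mean effect, and D the mean effect in the other children. The article gives neither f nor e, so both are varied.

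- Mean effect over all children: d = D(1 − f) + e·f
- SD in the active arm with mixture variance: √(8.4² + f(1 − f)(D − e)²); the sham arm keeps 8.4

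Evaluable children: 30 × 0.9 = 27, taken as 13 active and 14 sham (25 degrees of freedom). Power is from the noncentral t with standard error √(SD²active/13 + 8.4²/14). The column 'SD 8.4' leaves out the mixture variance.

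| D (min) | e (min) | f | d (min) | Active SD | Power, SD 8.4 | Power, mixture SD |
|---|---|---|---|---|---|---|
| 10 | – | 0% | 10.0 | 8.40 | 84% | 84% |
| 10 | 0 | 10% | 9.0 | 8.92 | 76% | 74% |
| 10 | 0 | 20% | 8.0 | 9.30 | 66% | 61% |
| 10 | 0 | 30% | 7.0 | 9.57 | 55% | 49% |
| 10 | 0 | 40% | 6.0 | 9.72 | 43% | 38% |
| 10 | 5 | 10% | 9.5 | 8.53 | 81% | 80% |
| 10 | 5 | 20% | 9.0 | 8.63 | 76% | 75% |
| 10 | 5 | 30% | 8.5 | 8.71 | 71% | 70% |
| 17.88 | 0 | 10% | 16.1 | 9.97 | >99% | 99% |
| 17.88 | 0 | 20% | 14.3 | 11.03 | 99% | 95% |
| 17.88 | 0 | 30% | 12.5 | 11.73 | 96% | 86% |
| 17.88 | 0 | 40% | 10.7 | 12.14 | 89% | 72% |

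With D = 17.88 and e = 0, the mean effect stays at or above 10 min up to f = 1 − 10/17.88 = 44%.

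**3. If all 30 are evaluable (15 per arm), D = 10.** Power is 88% at f = 0. With e = 0 it is 78–81% (f = 10%), 67–71% (20%) and 54–60% (30%). With e = 5 it is 80–81% (20%) and 75–76% (30%).

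**4. How much room is there?** As an illustration only, suppose waking-only children had baseline latency spread evenly over 0–20 min, with mean 10 min. A mean fall of 10 min would then need every latency to reach zero. With a mean baseline above 10 min it is arithmetically possible.

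**The case against.** The strongest reply is that 10 min is presented as the minimally important difference, not as the expected effect. The cited reductions start at 17.88 min. If children with prolonged latency gain that much, the trial keeps good power with up to 30% waking-only children who gain nothing. This stands as a limit on the concern, with one reservation: the article does not say whether those reductions are net of sham.

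A reader might infer that waking-only children cannot shorten latency by 10 min on average, or that the 80% holds only if practically all children have prolonged latency. The documents support neither. Latencies of 10–20 min are compatible with waking-only entry, as are longer ones on up to two nights a week. The table also shows cases with adequate power in a mixed sample. Nor is the 80% a calculation error.

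It can also be said that Trial status plans to continue until 30 children have completed treatment and the pre- and post-measurements, so 27 evaluable is pessimistic. That is fair. The larger number lifts every figure, but with D = 10 and e = 0 power is still about 67–71% at a 20% share.

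The broad entry rule fits the stated interest in insomnia generally, and the trial calls itself a pilot. Both are true, but the article also states an efficacy aim and makes a formal power claim, so the condition behind that claim should be visible.

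Finally, baseline latency is already in the model. It is there as a repeated outcome, however, and not as a covariate for end-of-treatment latency.

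**Conclusion.** The mismatch is real and lies in the current text: entry does not require prolonged latency, while sizing and testing concern latency alone. The 30 and the 80% are correct for a 10-min mean effect over all randomised children, but the entry rule does not secure that mean.

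The size of the loss is uncertain because f and e are assumptions. With 27 evaluable children and 10 min in the others, power is about 61–66% (f = 20%) and 49–55% (f = 30%) if e = 0, and 75–76% and 70–71% if e = 5 min. It stays at or above 86% up to f = 30% with e = 0 if the others gain 17.88 min. The point is therefore an unstated condition on the power and a risk to the reading of a null result. It does not show that the trial is underpowered.

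**What to change.** 1. In Sample size, state that the 80% power assumes a 10-min mean effect over all randomised children, including those who enter on waking alone, and show the range above with f and e labelled as assumptions.
2. In Statistical analysis, add baseline PSG latency as a covariate in the primary analysis of end-of-treatment latency. Baseline is then no longer also an outcome time point in that analysis. This sharpens the comparison and absorbs chance imbalance in baseline latency, but it does not undo the dilution.
3. Pre-specify the treatment effect in children with baseline latency above 20 min as a supportive analysis, reported alongside PSG wake time after sleep onset. The main comparison stays with all randomised children.

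The cost is wording and one added analysis on data already collected. The downsides are a less favourable stated power and a small, imprecise subgroup. Re-stratifying the envelopes midway is not needed: recruitment is under way, and two lists within 30 children would leave few per stratum for little gain.
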